**Methods:**

This RCT has received approval from The Conjoint Health Research Ethics Board (CHREB) of the University of Calgary (Ethics ID # E-24476). Twenty-four participants treated for a malignancy with autologous stem cell transplant (5 to 18 years) in the Alberta Children’s Hospital will be randomly assigned to an exercise or control group. The exercise group will participate in a two-phase exercise intervention (in- and outpatient) from hospitalization until 10 weeks after discharge. The exercise program includes strength, flexibility and aerobic exercise. During the inpatient phase this program will be performed 5 times/week and will be supervised. The outpatient phase will combine a supervised session with two home-based exercise sessions with the use of the Wii device. The control group will follow the standard protocol without any specific exercise program. A range of outcomes, including quantitative and functional recovery of immune system, cytokine levels in serum, natural killer (NK) cells and their subset recovery and function, and gene expression of activating and inhibitory NK cell receptors, body composition, nutrition, quality of life, fatigue, health-related fitness assessment and physical activity levels will be examined, providing the most comprehensive assessment to date.

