**Figure 2 F2:**
[figure not shown]
SCORE study protocol.

The second phase will be a 10-week outpatient intervention, beginning once the child is discharged. We will utilize a mixed EX program, including supervised (at the University of Calgary) and home-based training incorporating the use of the Nintendo ® Wii device™ (Wii Fit, Wii Dance and Sports™ games).

Assessments include measures of QOL, fatigue, health-related fitness (HRF), physical activity levels and hematological and immunological reconstitution. Assessments will be completed at baseline, 30, 85 and 180 days post infusion day (day 0+). Hematological and immunological reconstitution will be assessed at the time points described above, plus at 7, 15 and 56 days post reinfusion. The baseline assessment will be completed within the two-month period prior to the conditioning regimen. The 30 day assessment is intended to capture the effect of Phase 1, the EX program during the hospitalization period (from conditioning regimen up to discharge). The 85 day assessment is intended to capture the early survivorship recovery period after an autologous SCT and the effect of Phase 2, EX program during the outpatient phase. The 180 day assessment will provide a mid-term follow-up of physical activity, QOL, fatigue and hematological and immunological reconstitution. These outcomes will allow us to examine the impact of an EX program implemented early during the SCT process 3 months after finishing the EX intervention on (i) physical activity levels (ii) QOL and fatigue iii) hematological and immunological recovery

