#### Control group

These subjects will not participate in any scheduled EX and will perform the same battery of tests as the intervention group. They will be offered an EX program upon completion of phase 2, to be held in the Thrive Centre, University of Calgary.

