### Sample size

Power calculations were derived using GPower 3.1 [19] The sample size/power calculation was based on relevant intervention literature [12,20,21] with natural killer cell activity as the primary outcome measure (Cohen’s d = .79). With an α of .05 and power of .80, a minimum sample size of 20 participants is required. To account for potential drop out, we will recruit an additional 20%, for a total of 24 participants.

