### EX intervention 

This RCT will be a biphasic EX intervention.

Phase 1 – The inpatient phase will be performed at the ACH during conditioning and the isolated phase of autologous SCT.

Phase 2 – The outpatient phase will take place after discharge. The participants will participate in a 10 week mixed supervised and home-based EX program utilizing the Wii device.

In both phases participants will wear a portable heart rate monitor (RS300X Polar) when at the EX sessions to ensure safety and target the aerobic EX intensity between 50% and 70% of heart rate reserve (HRR), depending on the physical status of each child.

The training session will be cancelled if the child has platelet levels below 10.000/ μl, hemoglobin levels below 8 g/dl, fever greater than 38°C, pain, diarrhea, hemorrhage or any other complication(s) the oncologist thinks may worsen with EX. Additionally, a session may be cancelled if the child doesn’t want to participate.

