### Hematological and immunological recovery

#### Specimen collection

At baseline 2 Buccal Swabs will be collected to use for deoxyribonucleic acid (DNA) extraction. DNA specimens will be used to perform genotyping of activating and inhibitory KIR genes. The patient should not eat or drink anything for one hour prior to the specimens being taken. We will take one swab and rub the inside of right and left patient’s cheek for approximately 10 seconds. The swab will air dry for 1-2 minutes prior to replacing it into its container.

The baseline blood draw will be performed at the Unit 1 in the ACH (within 7 days prior to conditioning and transplant). The maximum blood volume to be drawn will be determined based on patient weight and other ordered blood work. A minimum of 7 mL will be required. The blood sample collection will be performed at baseline, day 7, 14, 30, 56, 85 and 180.

To avoid any acute EX effects, we will discourage any specific EX training 24 h before blood draws in the samples that will be collected at baseline and after transplant on day 14, 30, 56, 85 and 180. Research samples may be collected via central line or peripheral draw. For this study, we will store 1 aliquot each for peripheral blood mononuclear cells (PBMNCs) for every blood specimen serum. The aliquoted serum samples will be stored in our -86°C freezers and PBMNCs will be cryo-preserved at -150°C using liquid nitrogen based cell storage facility. All immune functional assays will be performed on cry preserved PBMNCs.

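### The 24-hour no-training rule covers every scheduled blood draw except day 7, so an acute exercise effect can enter that sample in the exercise arm only

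*Protocol article*

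**What the plan says.** Under Specimen collection, the protocol article sets out seven draws: "The blood sample collection will be performed at baseline, day 7, 14, 30, 56, 85 and 180". The next paragraph of the same section gives the pre-draw rule and its purpose: "To avoid any acute EX effects, we will discourage any specific EX training 24 h before blood draws". It then limits the rule to draws "in the samples that will be collected at baseline and after transplant on day 14, 30, 56, 85 and 180".

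The Study design section confirms that day 7 is an immune assessment and not only a clinical blood test: "Hematological and immunological reconstitution will be assessed at the time points described above, plus at 7, 15 and 56 days post reinfusion".

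On exposure by arm, the abstract says of the exercise group: "During the inpatient phase this program will be performed 5 times/week and will be supervised". The EX intervention section gives the timing: "The inpatient phase will be performed at the ACH during conditioning and the isolated phase of autologous SCT". Study design has this phase continue until discharge. For controls: "These subjects will not participate in any scheduled EX and will perform the same battery of tests as the intervention group".

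The Sample size section is built "with natural killer cell activity as the primary outcome measure" and names no time point for it. Data analysis plans doubly multivariate repeated measures ANOVA to compare the arms and excludes no time point.

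**The concern.** The rule exists because the authors hold that a recent session can disturb the immune readouts. That premise is the protocol's own. On that premise, the one draw left outside the rule is the first after transplant, when training is at its most frequent.

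Exposure to a recent scheduled session is tied to arm: possible for exercise children, absent for controls. An acute effect at day 7 would therefore not be noise shared by both arms. It would be a between-arm difference that the data cannot separate from faster or slower immune recovery, which is the primary objective. Day 7 is also the first post-transplant point of the recovery curve. If the time since the last session is not recorded when blood is drawn, it may not be possible to reconstruct it reliably later.

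**Working it through.** **1. Compare the two lists** (both under Specimen collection).

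| Draw | Scheduled | Under the 24-hour rule |
|---|---|---|
| Baseline | yes | yes |
| Day 7 | yes | **no** |
| Day 14 | yes | yes |
| Day 30 | yes | yes |
| Day 56 | yes | yes |
| Day 85 | yes | yes |
| Day 180 | yes | yes |

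Scheduled draws minus covered draws leaves day 7 alone; nothing is covered that is not scheduled. So 6 of 7 draws fall under the rule. No other section extends the rule to day 7, explains the omission, or sets day 7 apart in the analysis.

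**2. Exposure at day 7.** Inputs: 5 inpatient sessions a week (abstract), no scheduled exercise in controls (Control group), 12 children per arm (Study population). Assume at most one session a day, with sessions and draws spread evenly over the week.

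- No cancellations: share with a session in the preceding 24 h = 5/7 = 0.714, or 12 × 0.714 = 8.6 exercise children on average.
- Half the sessions held: 0.5 × 5/7 = 0.357, or 12 × 0.357 = 4.3 children.
- Controls: 0 from scheduled training.

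The EX intervention section lists many grounds for cancelling a session (blood counts, fever, pain, diarrhea, hemorrhage, other complications, the child's wish) but gives no rate. The half-held case is therefore an assumption.

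**3. Illustrative size for a day-7 comparison.** The documents give no size for an acute effect, so let a recent session shift a readout by δ SD, with δ from 0.2 to 1.0 assumed. The expected spurious arm difference is share × δ. The false-positive rate comes from simulating 12 v 12 normal outcomes of unit SD, no true recovery effect, each exercise child exposed at random with the given share, and a two-sided t-test at 0.05.

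| Share exposed | δ (SD) | Spurious difference (SD) | False-positive rate |
|---|---|---|---|
| 0.714 | 0.2 | 0.14 | about 6% |
| 0.714 | 0.5 | 0.36 | about 13% |
| 0.714 | 1.0 | 0.71 | about 36% |
| 0.357 | 0.2 | 0.07 | about 5% |
| 0.357 | 0.5 | 0.18 | about 7% |
| 0.357 | 1.0 | 0.36 | about 12% to 13% |

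The half-held rows use a share of 0.357. Taking half the *children* as exposed (share 0.5) is a different case: it corresponds to 0.5 / 0.714 = 70% of sessions being held.

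**4. What cannot be calculated.** The planned analysis is a multivariate repeated-measures comparison over several time points. Its behaviour depends on correlations between visits and outcomes that the document does not give. The protocol has no figure of its own on this point to reproduce.

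**The case against.** The strongest reply is that the mismatch is small and its effect unproven.

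- **Possibly a slip.** The same schedule reads day 15 in Study design and day 14 in Specimen collection, so the lists were not closely checked. A slip still leaves a rule that, followed as printed, does not cover day 7.
- **Possibly deliberate**, for example to avoid losing an inpatient session. The article does not say so, and it keeps day 7 in the comparison.
- **Cancellations.** All children receive myeloablative conditioning and the grounds for cancelling are broad, so actual exposure at day 7 may be well under 71%. This stands, and it is why that figure is given only as an upper value.
- **The assumed shift.** Nothing in the documents supports any particular δ. At 0.2 SD the effect is slight even at full exposure. This stands too.
- **One time point of seven, and not the planned test.** The weight of day 7 in the primary result cannot be determined, since no time point is fixed for NK activity.
- **The contrast with other draws is not absolute.** The rule only discourages training, so the listed draws are not firmly protected, and at baseline it matters little because that draw precedes the programme.

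These points limit the size of the problem. None supplies a reason for the omission or removes the link between arm and exposure.

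**Conclusion.** The omission is certain on the text. Its consequence is a possibility that the plan leaves open: at day 7, and only there among the scheduled draws, the written rule does not discourage training in the preceding 24 hours, and a resulting acute effect would fall on the exercise arm alone.

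The size rests on assumptions. The 71% needs an even spread of sessions and draws and no cancellations; the weekdays of sessions and infusions are not given. The range of about 6% to 36% at full exposure, or about 5% to 13% with half the sessions held, needs an assumed shift of 0.2 to 1.0 SD and a stand-alone day-7 test.

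A reader might infer that the trial's primary false-positive rate rises to as much as 36%, or that most exercise children will in fact have trained the day before. The documents support neither: the first describes a test the protocol does not plan, and the second ignores cancellations of unknown frequency. Nor should the assumed shift be set against the design effect of 0.79, which belongs to NK activity and not to any readout at day 7. A further inference, that serum cytokines would carry the effect whatever the cell counts at day 7, has no support in the text. The point merits correction mainly because the correction is nearly free.

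**What to change.** Reconcile the two lists under Specimen collection so that day 7 falls under the same pre-draw rule as the other samples. Add one field to the sample form for hours since the last exercise session, completed at every draw in both arms. Because the rule only discourages training, this field also shows how well it was followed at the other draws.

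If day 7 was left out on purpose, state the reason and keep the day-7 values out of the arm comparison, reporting them descriptively.

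The cost is a short text correction, one form field, and at most one inpatient session per child re-timed. No sample size or power figure changes. The day 14 and day 15 labels for the next draw could be aligned in the same edit; that is a separate discrepancy and does not affect this point.

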#### Hematological and immune system assessment

Assessment of the impact of the EX intervention on the immune recovery of pediatric autologous SCT patients will be based on four parameters (a) Recovery of different leukocyte cell subset (e.g., T cells, NK cells, B cells, monocytes, neutrophils etc) in peripheral blood, (b) Expression of activating and inhibitory KIRs (c) Function of NK cells and their subsets and (d) Levels of different pro-inflammatory and regulatory cytokines in serum,

a) Recovery of NK cells and other immune cells subsets will be performed by flow cytometry enumeration of different blood leukocyte subsets including NK cells and its subsets (cytolysis and regulatory NK cells), T cells and its subsets (CD4, CD8, regulatory, naive and memory T cells), B cells, monocytes, neutrophils and dendritic cells.

b) Gene/allele carriage analysis for 8 inhibitory KIR genes (2DL1, 2DL2, 2DL3, 2DL4, 2DL5, 3DL1, 3DL2 and 3DL3); 6 activating KIR genes (3DS1, 2DS1, 2DS2, 2DS3, 2DS4 and 2DS5) and two pseudo genes (2DP1 and 3DP1) will be performed for all 24 patients. Gene expression analysis of 14 KIR genes will be done by RNA based real-time PCR analysis. Total RNA will be extracted from the PBMNCs for each time point and cDNA will be prepared using random primers and M-MLV reverse transcriptase enzyme. A quantitative real time PCR analysis will be performed to assess the expression of genes encoding for 8 inhibitory and 6 activating KIR genes. Quantitative PCR will be carried out with SYBR Green PCR method. The mRNA expression of different KIR genes will be normalized against GAPDH, and fold change in expression will be determined using ddCt method. Additionally, a flow-cytometry based protein expression analysis for 7 KIRs (4 activating and 3 inhibitory KIRs) on NK cells will also be performed. PBMNCs from each subject for each time point will be stained with fluorochrome labeled antibodies against different KIR molecules and markers specific for NK cells. Cells will be analyzed by multi-color flow cytometry. To quantify the amount of KIR expression on NK cells, we will determine the mean fluorescence intensity (MFI) for each KIR on NK cells.

c) NK function will be assessed by measuring in vitro cytokine secretion and degranulation by different NK cell subsets (cytolysis and regulatory NK cells) on incubation with K-562 cell lines. PMNCs will be cultured with and without K562 cell in RPMI supplemented with 5% fetal bovine serum, glutamine (2 mM), Penicillin (100 U/ml) and Streptomycin (0.1 mg/ml) at 37°C in a humidified atmosphere containing 5% CO_2_. To measure degranulation, fluorochrome-conjugated antibody against human CD107a (a surrogate marker of degranulation) will be added to the cells at the start of culture as CD107a is only transiently expressed on T cell surface following activation-induced degranulation and it becomes internalized over time. Monessen will also added to the culture from beginning to ensure blockade of cytokine export from cells to the extra-cellular space and to provide neutral pH that maintains the fluorescence of FITC-conjugated CD107a antibody bound to CD107a, when internalized into the cell. At the end of the culture, cells will be stained with fluorochrome labeled antibodies against CD, CD3, CD56, CD16 and IFNγ and will be analyzed by multi-color flow cytometry. A cytolysis NK cell will be defined as CD3^neg^ CD56^dim^ CD16^pos^ NK cell while a regulatory NK cell will be defined as CD3^neg^ CD56^dim^ CD16^pos^ IFNγ^pos^ NK cell. Positivity for IFNγ and CD107a will correspond to the cytokine producing and degranulation functions respectively.

d) Assessment of cytokine levels in serum: A total of 30 cytokines including TNF-α, IFN-γ, IL-10, IL-6, IL-1α, IL-1β, IL-1R, IL-2, IL-12, TGF-β IL-15, and IL-17 etc will measured in the serum specimens for each time point using a bead-based array on Luminex.

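### KIR mRNA is measured in unsorted PBMNCs and normalised only to GAPDH, so a between-arm difference in NK share would read as a difference in KIR expression

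*Protocol article*

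**What the plan says.** The section Hematological and immune system assessment bases the immune effect of exercise on four parameters. Parameter (a) is cell recovery: "Recovery of NK cells and other immune cells subsets will be performed by flow cytometry enumeration of different blood leukocyte subsets". Parameter (b) is listed separately: "b) Expression of activating and inhibitory KIRs".

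For parameter (b) the section fixes three things:

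- Scope: "Gene expression analysis of 14 KIR genes will be done by RNA based real-time PCR analysis". The genes are 8 inhibitory and 6 activating.
- Material: "Total RNA will be extracted from the PBMNCs for each time point and cDNA will be prepared using random primers and M-MLV reverse transcriptase enzyme". No NK-cell isolation step is described.
- Normaliser and metric: "The mRNA expression of different KIR genes will be normalized against GAPDH, and fold change in expression will be determined using ddCt method".

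A second readout is added at protein level: "a flow-cytometry based protein expression analysis for 7 KIRs (4 activating and 3 inhibitory KIRs) on NK cells will also be performed". It is quantified as MFI on NK cells, in PBMNCs stained with NK-cell markers for each subject and time point.

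The article does not say that the NK counts or the NK-marker staining are used to adjust or interpret the mRNA fold change. The abstract and the Background describe KIRs as receptors of NK cells. Theme 1 of the Discussion raises the possibility that physical activity modulates KIRs.

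**The concern.** The article treats KIRs as NK-cell receptors, yet the mRNA is taken from a mixture of which NK cells are only a part. The denominator, GAPDH, is contributed by all cells in the mixture. The ratio therefore depends on two things: how much KIR mRNA each NK cell makes, and what fraction of the PBMNCs are NK cells.

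That fraction may move in this trial. Patients receive myeloablative conditioning and are sampled repeatedly up to day 180, while their leukocyte subsets recover. Recovery of those subsets is itself an outcome that exercise is meant to influence. Randomisation does not protect against this, because NK share is measured after randomisation and may be affected by the intervention.

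At stake is the reading of parameter (b). If exercise changes the NK share relative to control, the mRNA result would move with it, and the trial could report KIR modulation where only cell composition differs. Parameters (a) and (b) would then not be independent evidence.

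**Working it through.** The article gives no figure to reproduce on this point. The check asks what the planned ratio shows when KIR expression per NK cell is the same in both arms.

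**Inputs from the article** (Hematological and immune system assessment): RNA from unsorted PBMNCs; GAPDH as the only normaliser; ddCt fold change; 14 genes by mRNA (8 inhibitory, 6 activating); 7 KIRs by flow on NK cells (3 inhibitory, 4 activating).

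**Inputs that are assumptions**, because the article does not give them:

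- f, the NK share of PBMNCs: illustrative values from 5% to 22%.
- r, GAPDH mRNA per NK cell relative to other PBMNCs: 0.5 to 2.
- b, KIR mRNA per non-NK cell relative to an NK cell: 0 to 5%.

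**Step 1: the signal.** With KIR mRNA per NK cell held constant,

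S(f) = [f + (1 − f)·b] / [f·r + (1 − f)].

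The apparent between-arm ratio is S(f_exercise) / S(f_control). With r = 1 and b = 0 the denominator is 1, and the ratio reduces to f_exercise / f_control.

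**Step 2: numbers, with true per-cell expression identical in both arms.**

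| NK share, control vs exercise | r = 1, b = 0 | Range over r = 0.5 to 2, b = 0 to 5% |
|---|---|---|
| 10% vs 10% | 1.0 | 1.0 |
| 20% vs 22% | 0.22/0.20 = 1.1 | 1.06 to 1.11 |
| 10% vs 20% | 0.20/0.10 = 2.0 (ddCt −1) | 1.52 to 2.11 |
| 10% vs 5% | 0.05/0.10 = 0.50 (ddCt +1) | 0.49 to 0.70 |

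The range ends for 10% vs 20% are:

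- r = 0.5, b = 0: (0.20/0.90) / (0.10/0.95) = 2.11.
- r = 2, b = 0.05: (0.24/1.20) / (0.145/1.10) = 1.52.

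The range ends for 20% vs 22% are:

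- r = 0.5, b = 0: (0.22/0.89) / (0.20/0.90) = 1.11.
- r = 2, b = 0.05: (0.259/1.22) / (0.24/1.20) = 1.06.

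**Step 3: what cancels.** With r = 1 and b = 0, log2 S(f) = log2 f, apart from a constant for per-cell expression. A change in share that is the same in both arms adds the same amount to each arm's mean log2 value and drops out of the difference. Only a between-arm difference in share remains. A doubling of share over time in both arms would thus give a 2-fold change within each arm and a ratio of 1.0 between arms.

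**Step 4: coverage by the NK-restricted assay.** Taking each stained KIR as the product of one of the 14 genes, 8 − 3 = 5 inhibitory and 6 − 4 = 2 activating genes remain. So 5 + 2 = 7 genes have no per-NK-cell measure.

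**The case against.** The strongest reply is that the article already gives the per-NK-cell question to another assay. MFI is determined on NK cells, while the mRNA sentence never claims to be per cell. NK enumeration and NK-marker staining are planned, and a condensed article may leave an adjustment to a fuller document. KIR mRNA is also one of two readouts within one of four parameters, in a study that describes its data as pilot. The sample size rests on NK-cell activity, which is not affected, and neither is MFI.

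Part of this stands. The point concerns the mRNA readout only, and its consequence is limited. It does not dispose of the point: source, normaliser and metric are all stated, and it is their combination that mixes composition with regulation. MFI helps for 7 KIRs, and nothing gives it precedence over the mRNA result.

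A reader might also infer more than the article supports:

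- *That faster NK recovery alone would produce apparent up-regulation.* The artefact follows NK share, not NK count. If exercise speeds recovery of all mononuclear subsets in proportion, the count rises, the share does not, and the ratio stays at 1.0. The article predicts no shift in share.
- *That a 2-fold or larger rise in share over time is the bias in the exercise effect.* Such a rise common to both arms cancels on the log scale. For a 2-fold bias, exercise would have to double the NK share relative to control, and nothing in the article suggests that.
- *That proportionality follows from the normalisation alone.* It also needs equal GAPDH per cell type and no KIR signal from non-NK cells. Neither is stated, hence the ranges above.

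**Conclusion.** The point holds as a limited flaw in a stated method. As planned, the KIR mRNA readout cannot separate a between-arm difference in the NK share of PBMNCs from a difference in KIR expression per NK cell. For at least 7 of the 14 genes no other planned measure resolves this.

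The size in this trial cannot be known from the article. The apparent between-arm ratio is roughly the ratio of NK shares, so a small difference in share gives a small artefact and only a large one would mislead seriously. The artefact can run in either direction. These statements rest on the assumed values of f, r and b; that the artefact exists whenever shares differ, and its direction, held throughout the ranges tried. The documents do not support saying that false up-regulation is expected, or that it would be 2-fold or more.

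**What to change.** - Analyse ddCt on the log2 scale, so that changes in share common to both arms cancel in the group comparison.
- Report the unadjusted result as KIR transcript abundance in PBMNCs, not as KIR expression by NK cells.
- Beside it, report an analysis adjusted for the NK fraction of the same PBMNC sample. The planned staining with NK-cell markers at each time point should supply that fraction without new sampling.
- Base any claim that exercise modulates KIRs on the adjusted analysis and, for the 7 KIRs that have it, on MFI on NK cells.

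The cost is some extra analysis of data already planned. The adjustment adds noise at early draws with few NK cells. It is also only approximate if GAPDH content differs by cell type or non-NK cells express KIRs, so it should accompany the bulk result and not replace it as an exact correction.

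### Regulatory NK cells are defined as the IFNγ-positive part of the cytolysis subset, so the two subsets overlap and the IFNγ-positive share within the regulatory subset is 100% by definition

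*Protocol article*

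**What the plan says.** All the relevant text is in the protocol article, section Hematological and immune system assessment.

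- Part (a), on recovery of cell numbers, lists counts by flow cytometry "including NK cells and its subsets (cytolysis and regulatory NK cells").
- Part (c) says that NK function will be assessed by "measuring in vitro cytokine secretion and degranulation by different NK cell subsets (cytolysis and regulatory NK cells").
- The culture conditions in (c) are: "PMNCs will be cultured with and without K562 cell in RPMI".
- Part (c) then defines the first subset: "A cytolysis NK cell will be defined as CD3^neg^ CD56^dim^ CD16^pos^ NK cell".
- The same sentence defines the second: a "regulatory NK cell will be defined as CD3^neg^ CD56^dim^ CD16^pos^ IFNγ^pos^ NK cell".
- The next sentence names the readouts: "Positivity for IFNγ and CD107a will correspond to the cytokine producing and degranulation functions respectively".

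No other place in the article gives a different phenotype for either subset.

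**The concern.** Measuring a function by subset presupposes two populations that can be told apart without using that function. Here the regulatory population is picked out by the function itself. IFNγ positivity decides whether a cell is regulatory, and IFNγ positivity is then the cytokine result for regulatory cells.

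Three things are at stake. First, the cytokine readout of the regulatory subset, taken as a percentage of that subset, carries no information about exercise. Second, a rise in IFNγ production by cytolysis cells would be reported as a rise in regulatory cell number, so a change in function would be read as a change in recovery. Third, the two subsets cannot be compared as separate populations, because one lies wholly inside the other. NK function and NK subset recovery are both among the parameters on which the article bases its assessment of immune recovery.

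**Working it through.** This is a question of definition. The article states no figure to reproduce, so the check is set logic.

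**Inputs, all from part (c)**

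| Item | CD3 | CD56 | CD16 | IFNγ |
|---|---|---|---|---|
| Cytolysis NK cell | neg | dim | pos | no condition |
| Regulatory NK cell | neg | dim | pos | pos |
| Readout of cytokine function | – | – | – | pos |
| Readout of degranulation (CD107a pos) | – | – | – | no condition |

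**Step 1: overlap.** Let C be the cytolysis cells and R the regulatory cells. By the definitions, R = C ∩ {IFNγ pos}. To confirm this, take every combination of CD3 (2 levels), CD56 (neg, dim, bright: 3), CD16 (2), IFNγ (2) and CD107a (2), which makes 2 × 3 × 2 × 2 × 2 = 48 combinations.

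- 4 combinations meet the cytolysis definition.
- 2 combinations meet the regulatory definition.
- Both regulatory combinations are among the 4, and none lies outside them.

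R is therefore a proper subset of C.

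**Step 2: cytokine readout within each subset.**

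- Regulatory: |R ∩ IFNγ pos| / |R| = |R| / |R| = 1 whenever |R| > 0. With no such cell the share is undefined.
- Cytolysis: |C ∩ IFNγ pos| / |C|. Of the 4 combinations, 2 are IFNγ positive, so this share is free to vary.

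**Step 3: ratio of the subsets.** |R| / |C| = |C ∩ IFNγ pos| / |C|, which is exactly the IFNγ response of the cytolysis subset.

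**Step 4: illustration.** The shares below are assumed; the article gives none. Take 1,000 cytolysis cells.

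| IFNγ-positive share of cytolysis cells | Regulatory count | Sum if the subsets are added | Counted twice | IFNγ-positive share of regulatory cells | Regulatory/cytolysis ratio |
|---|---|---|---|---|---|
| 5% | 50 | 1,050 | 50 | 100% | 0.05 |
| 20% | 200 | 1,200 | 200 | 100% | 0.20 |
| 50% | 500 | 1,500 | 500 | 100% | 0.50 |

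Suppose the first row is the culture without K562 and the second the culture with it. The cytolysis subset then shows a response of 20 − 5 = 15 percentage points. The regulatory subset shows 100 − 100 = 0. The same holds if the two rows are the two arms.

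**Step 5: what survives.** CD107a enters neither definition. Of the 4 cytolysis combinations 2 are CD107a positive, and of the 2 regulatory combinations 1 is, so degranulation can vary in both. IFNγ as a share of all NK cells can vary too.

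**The case against.** Several points on the other side are fair.

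- **Scope.** A reader might infer that the whole cytokine-function outcome is void. It is not. The 100% applies to one quantity, the IFNγ-positive share within the regulatory subset. This stands.
- **Denominator.** The article says only that positivity corresponds to each function. It does not say whether the result is a percentage of the subset, a percentage of all NK cells or a count. The zero difference follows only for a percentage of the regulatory subset. With another denominator the figure can vary, but it then reports the IFNγ-positive cytolysis cells under a second name. This makes the size conditional and leaves the overlap untouched.
- **Sample size.** A reader might infer that the power calculation is compromised. The Sample size section works "with natural killer cell activity as the primary outcome measure (Cohen’s d = .79"), and nothing there ties that outcome to the regulatory gate. The link is not supported.
- **Counts in part (a).** A reader might infer that regulatory cells cannot be enumerated there, because IFNγ staining is described only at the end of the culture in (c). Part (a) does not say that it uses the IFNγ gate. What can be said is that it uses the same label and that the only definition of that label is the one in (c).
- **Slip of the pen.** The antibody list in (c) includes a CD with no number, so a drafting error is plausible. That supports correcting the definition but does not remove the problem, because a laboratory following the text would apply this gate.
- **Detail left to a fuller document.** An article may leave gating to a laboratory manual. Here, however, the gate is stated, and the stated gate is what fails.

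**Conclusion.** The point holds as a local error of definition. The regulatory subset is nested entirely in the cytolysis subset. Its own IFNγ-positive share is 100% in any sample that contains such cells, so it cannot differ between arms, visits or culture conditions. The regulatory/cytolysis ratio duplicates the cytolysis IFNγ response.

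The overlap and the ratio follow from the text alone. The zero difference assumes that cytokine function is expressed as a percentage of the subset. The illustrative 5%, 20% and 50% are assumptions, and the conclusion does not depend on them.

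The finding does not reach IFNγ in the cytolysis subset or in all NK cells, CD107a in either subset, the other immune parameters or the sample size. The documents also do not show which regulatory phenotype was intended, so none can be read out of them.

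**What to change.** Define both subsets in part (c) by surface markers only, and make them mutually exclusive. The CD3, CD56 and CD16 antibodies already in the panel allow this, for example by separating the subsets on CD56 intensity and CD16. That example is a suggestion, and the investigators should confirm the exact regulatory phenotype.

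Remove IFNγ from the definition of any subset. Keep IFNγ and CD107a solely as function readouts within each subset, and state the denominator. Say in part (a) that the subset counts use the same surface gates.

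The cost is a changed gating definition. It needs no new reagent, sample or visit, and is best settled before any cells are gated.
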